## Abstract

**Background:**

Simultaneous pancreas kidney transplantation (SPK), pancreas transplantation alone (PTA) or pancreas transplantation after kidney (PAK) are the only curative treatment options for patients with type 1 (juvenile) diabetes mellitus with or without impaired renal function. Unfortunately, transplant waiting lists for this indication are increasing because the current organ acceptability criteria are restrictive; morbidity and mortality significantly increase with time on the waitlist. Currently, only pancreas organs from donors younger than 50 years of age and with a body mass index (BMI) less than 30 are allocated for transplantation in the Eurotransplant (ET) area. To address this issue we designed a study to increase the available donor pool for these patients.

**Methods/Design:**

This study is a prospective, multicenter (20 German centers), single blinded, non-randomized, two armed trial comparing outcome after SPK, PTA or PAK between organs with the currently allowed donor criteria versus selected organs from donors with extended criteria. Extended donor criteria are defined as organs procured from donors with a BMI of 30 to 34 or a donor age between 50 and 60 years. Immunosuppression is generally standardized using induction therapy with Myfortic, tacrolimus and low dose steroids. In principle, all patients on the waitlist for primary SPK, PTA or PAK are eligible for the clinical trial when they consent to possibly receiving an extended donor criteria organ. Patients receiving an organ meeting the current standard criteria for pancreas allocation (control arm) are compared to those receiving extended criteria organ (study arm); patients are blinded for a follow-up period of one year. The combined primary endpoint is survival of the pancreas allograft and pancreas allograft function after three months, as an early relevant outcome parameter for pancreas transplantation.

**Discussion:**

The EXPAND Study has been initiated to investigate the hypothesis that locally allocated extended criteria organs can be transplanted with similar results compared to the currently allowed standard ET organ allocation. If our study shows a favorable comparison to standard organ allocation criteria, the morbidity and mortality for patients waiting for transplantation could be reduced in the future.

**Trial registration:**

Trial registered at:
NCT01384006

## Background

Patients with type 1 (juvenile) diabetes mellitus generally suffer from long-term complications, most of which are related to vascular disease. Associated nephropathy can lead to dialysis with its own major risk factors for cardiovascular disease and a low quality of life. Simultaneous pancreas kidney transplantation (SPK) or pancreas transplantation after kidney (PAK) are the only curative treatment options for type 1 diabetic patients with impaired kidney function
[1,2]. The aim of SPK is to optimize blood sugar control, prevent retinopathy progression and reduce other cardiovascular diseases, thereby restoring life quality and length
[3-5]. Indeed, if SPK can be done before the patient requires dialysis, the positive effects are even more dramatic
[6,7]. For instance, progressive retinopathy is halted or even reversed after SPK
[8] and PAK
[9], and motor and autonomous nerve functions improve
[10]. Pancreas transplantation alone (PTA) is restricted to patients with good renal function who suffer from brittle diabetes or frequent hypoglycemia; this is the only treatment option allowing non-uremic patients with brittle diabetes long-term insulin-independency.

Waitlists are constantly increasing in the Eurotransplant (ET) area. In 2000 there were 195 people on the waitlist for pancreas or islet cell transplantation, with a total of 331 transplantations performed in that year. In 2010 the waitlist increased to 337 patients, but only 249 transplantations were possible. Thus, time on the waitlist in Germany almost doubled within the last ten years and is now close to two years (data provided by ET), leading to a significantly worse outcome and higher morbidity for the patients. One major reason for this decline may be the fact that – with constantly increasing mean donor age - a large number of pancreas allografts potentially eligible for transplantation were excluded by the ET pancreas allocation system (EPAS) until December 2011. Those criteria excluded donors older than 50 years and those with a body mass index (BMI) ≥30 (ET Manual Version 26 May 2009). As the average age of a post-mortal organ donor in the ET area is now 58 years, donor selection by age has been a major factor contributing to the current donor pancreas shortage. In Germany (year 2009), the total number of deceased organ donors was 1,217. However, only 407 donors were at an acceptable age of < 50 years. Altogether, 594 patients were not even screened for pancreas donation due to age, regardless of all other medical conditions. In addition, approximately 13% of potential donors were not eligible for pancreas donation due to the BMI restriction (data provided by Deutsche Stiftung für Organtransplantation e.V. (DSO)). Moreover, in the ET-area pancreas grafts are allocated without local priority, frequently leading to rather long ischemic times due to transportation issues. In summary, because of the shortage of organ donors there is a critical need to use more of the available pancreas grafts for transplantation
[11].

Currently, available retrospective data from centers outside of the ET area suggest a similar outcome after transplantation using extended criteria organs; however, there is no prospective controlled trial addressing this issue. Therefore, the aim of our multicenter trial is to investigate the hypothesis that organs from donors 50 to 60 years old or with a BMI higher than 30, using local allocation with shorter ischemic times, can be transplanted with similar results compared to the standard criteria organs. The potential benefit for the patient who agrees to be transplanted with an extended donor criteria (EDC) pancreas (simultaneously with a standard kidney from the same donor) is a reduced waiting time with increased survival and life quality. This could mean that patients will be free from dialysis and insulin therapy earlier than presently expected in this region. We suggest that all pancreas transplantation programs in Germany (later, in the ET area) will benefit from this allocation system, as these EDC allografts will be available in addition to the pancreas grafts allocated currently, thereby increasing the pool of organs for pancreas transplantation. If the EXPAND study shows that EDC pancreases can be used with a regional allocation system without additional risk, this will potentially lead to a readjustment of pancreas allocation towards a regional allocation and transplantation system, which might achieve better results for more pancreas transplant recipients.

## Methods/Design

### Objectives and study concept

This study is a prospective, multicenter, single blinded, non-randomized, two-armed trial comparing outcome after SPK, PTA or PAK transplantation of organs with the currently allowed standard donor criteria to organs of donors with extended criteria. Extended criteria means a BMI 30 to 34 or donor age between 50 and 60 years. The enrollment phase will be three years with a follow-up period of one year. The primary endpoints are pancreas allograft survival and function at three months after transplantation. Our hypothesis is that pancreas organs of donors with extended criteria if transplanted regionally will have a similar function compared to organs with the currently allowed criteria. Overall survival, kidney and pancreas allograft function and survival, incidence of dialysis, post transplant insulin requirement, as well as infections and cardiovascular events will be assessed as secondary endpoints during the one-year follow-up. Secondary endpoints additionally include a quality of life assessment, biopsy proven acute rejections and time on the waitlist. In this study, patients who receive a standard criteria organ will be included in the control arm, and an equal number of patients who receive an EDC organ will be included in the study arm (Figure 
1).

### Allocation system

The allocation algorithm for potential deceased pancreas donors is regulated and defined in the ET handbook, section 7.1: Pancreas Allocation Algorithms. One reason for the decline in availability of pancreas allografts is the strict exclusion criteria set by the EPAS. As already mentioned, the main cut-off criteria for donors are age > 50 years or BMI ≥ 30 (current, standard criteria). For organs within the current criteria, allocation is performed according to HLA matching to the recipient, urgency status of recipient, waitlist time, and so on. Local distribution aspects are not part of the current allocation system, resulting in relatively long cold ischemic times in many cases.

For the EXPAND Study to allow allocation of EDC organs (age 50 to 60 or BMI 30 to 34) all responsible national and European authorities have been included in the development of an alternative rescue allocation system. ET and the German Medical Legislation Authorities, as well as the national Organ Procurement Organization (DSO) have been actively involved. In December 2010, ET established a rescue allocation system for extended criteria pancreas donors for the purposes of the EXPAND Study.

All deceased potential pancreas donors are screened for eligibility with regard to the current allocation al-gorithm. Organs meeting the standard criteria will be allocated to control arm patients. Other potential organs of donors with EDC who are between 50 and 60 years of age or have a BMI of 30 to 34 are now allocated according to the so-called ‘Beschleunigtes Vermittlungsverfahren’ (‘rescue allocation’), which has recently been implemented in the ET allocation system for extended pancreas use in Germany as part of this study. These organs are allocated only regionally to ensure a cold ischemic time of less than 12 hours. Other donor criteria are used to identify potential donors such as serum amylase or lipase, time on the ICU for the donor or use of vasoactive drugs; the risk/benefit assessment is made at the discretion of the transplant surgeons in both groups, with no distinct cut off line for those parameters.

Organ procurement and transplantation procedures are carried out according to internationally defined standards of organ procurement and pancreas transplantation. In Germany, arterial perfusion with histidine-tryptophan-ketoglutarate (HTK) solution is routinely performed and a backtable perfusion through the portal vein is recommended. In the case of an EDC organ, the regional allocation is performed with the following rules:

1. Regional centers receive organ offers in a rotation pattern. This means that every center receives (in a pre-defined fashion) sequential organ offers independent of the size of their waiting list or number of pancreas transplantations per year.

2. In case the first center rejects the offer, the organ is automatically offered to the procuring site.

The center receiving an offer can choose any (consented) recipient of the same ABO blood type, with a negative cross match, in their center for the transplantation. These rules aim for a fair local distribution, support small and very dedicated centers, and attempt to minimize cold-ischemic time.

### Study population

All patients on the waitlist for primary SPK, PTA or PAK meeting the inclusion criteria are eligible for the trial.

### Inclusion criteria

Adult patients >18 years of age eligible for primary SPK, PTA or PAK standard or extended criteria organ allocation are included in the study when informed consent is given prior to transplantation. In addition, the crossmatch testing must be negative.

### Exclusion criteria

Patients with malignant diseases within the past five years prior to transplantation (except for squamous cell carcinoma and basal cell carcinoma of the skin) are excluded. Patients who are listed for pancreas re-transplantation are excluded, as well as women of childbearing potential not willing to take contraception. Also, patients with a psychological, familial, sociological or geographic condition potentially hampering compliance with the study protocol and follow-up schedule, and patients under guardianship (for example, individuals who are not able to freely give their informed consent) are excluded.

### Consent

A study investigator will contact patients on the waitlist to introduce the study and associated procedures. An important part of the consent procedure is that the patient agrees to receive an extended criteria organ. When informed consent is given, patients are asked again for their consent at the time of transplantation. A patient is only eligible for an extended criteria organ when written and signed informed consent is given.

### Procedures to minimize bias

An important issue of this study was not only to confirm the safe use of EDC organs, but also to assess the quality of life experienced by the patient. To allow an unprejudiced evaluation, patients are blinded to their group inclusion. Because the transplant surgeon needs to consider all risk factors associated with the offered organ in relation to the patient, a double-blind set-up was not deemed appropriate. Additionally, randomization is not possible since inclusion into each study arm depends on the criteria (standard versus extended) of the organ, which is available for the patient at the time of transplantation.

### Interventions

#### Pre- and intraoperative data

Baseline data are documented, including demographics, medical history, current medication, liver and renal function, as well as history of renal replacement therapy and assessment of the quality of life. Intraoperative data (warm and cold ischemic times, blood-loss, requirement for blood products, incision to suture times) and donor data (age, serum-sodium, gamma- glutamyl transpeptidase, BMI, infectious status) are also documented.

#### Treatment regimen

Organ procurement and transplantation procedures are carried out according to internationally defined standards of organ procurement
[12] and pancreas transplant procedures
[1]. This trial is not aimed at establishing new immunosuppressive strategies, but rather to collect data prospectively in patients with EDC pancreas criteria, local allocation, and reduced cold-ischemic time in order to enlarge the donor pool for pancreas transplantation. To obtain comparable data, we strongly advocate the use of standardized immunosuppressive regimens in this study. We generally recommend the use of induction therapy with depleting or non-depleting antibodies
[13]. Further maintenance therapy is normally performed with a combination therapy of tacrolimus (Prograf®, Astellas Pharma GmbH, Munich, Germany) (center specific trough levels), primarily MMF i.v. (CellCept®, Roche Pharma AG, Grenzach-Wyhlen, Germany) and later MPA oral (Myfortic®, Novartis Pharma GmbH, Nürnberg, Germany) (enteric-coated MPA). Steroids can be used according to center-specific protocols. To reduce pro-diabetic effects, early withdrawal of steroids (for example, two weeks after transplantation) is recommended
[14]. Patients within the study will receive a combination immunosuppressive therapy of tacrolimus, MPA and steroids with early steroid withdrawal. Apart from this, all patients will be treated according to center specific standards. Transplant biopsies are not included within this protocol.

#### Follow-up

After transplantation, all patients will have follow-up study visits at days 7 and 14, and after 1, 3, 6, 9 and 12 months. Data collected in this study include only clinical and laboratory results that are routinely recorded anyway; investigations and examinations will not exceed the normal clinical standard at the participating sites. Documentation includes data on graft survival, graft function (laboratory values), incidence of clinically-diagnosed and biopsy-proven acute rejection (kidney and/or pancreas), severity of rejection (histological grade), changes in glucose metabolism, insulin requirement, need for dialysis, drug adverse events, infectious complications, cardiovascular incidents, general physical condition, and patient survival. At day 0 and at months 3, 6 and 12, a quality of life assessment will be performed (standardized questionnaire SF-12). During recruitment and follow-up of patients, regular monitoring of safety and endpoint data is performed according to good clinical practice (GCP) guidelines.

### Clinical sites

The study is planned as a multicenter (up to 20 sites) trial within Germany. As transplantation numbers in Germany are low for single centers, multiple sites are necessary to achieve the required patient number within a reasonable amount of time.

### Safety aspects

The Ethics Committee of the University Regensburg approved the study protocol on 17 December 2010 (number 10-101-0243), with approval following for all other participating sites. The study complies with the Declaration of Helsinki and the principles of GCP guidelines. Informed consent is obtained from each patient in written form while being on the waitlist and again prior to transplantation. A medical doctor familiar with the study informs the patient about the nature, duration and possible consequences of the trial. Patient safety and all potential threats for the patients are monitored once a year by an independent data monitoring committee. Qualified personnel at the sponsor site continuously review safety data, including adverse events and serious adverse events.

### Sample size calculation

The sample size was calculated by means of the primary endpoint, pancreas allograft survival rate after three months, on the assumption that a rate of 80% can be expected
[15,16] whereas, the minimal accepted survival rate is 65%. The limit of 65% is based on the maximally acceptable lower organ survival rate, as agreed by the clinical trial centers. The significance level of alpha (one-sided) was set to 0.05 and beta was set to 0.20. This is in accordance with the estimation of a one-sided 95% confidence interval for the survival rate after three months. Assuming that a one-sided, binomial hypothesis test with a target significance level α = 0.05 and a target power 1−β = 0.80 will be used for analysis, 55 patients with an extended donor pancreas allograft should be enrolled in this study. A sample size of 55 patients with extended donor pancreas allografts achieves 80% power to distinguish between the two proportions 65% (p_0_) and 80% (p_1_) using a one-sided, binomial hypothesis test with a target significance level of 0.05. The control group should be of equal size for analyzing the secondary endpoints. Assuming a maximal dropout rate of 10%, a total of 120 patients will be required. Sample size was estimated based on exact binomial probabilities and calculation was performed using NCSS-PASS 2000. No power analysis for secondary endpoints was done.

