## Discussion

A recent single center study showed a 20-year survival rate of 58% after SPK; in comparison, the 20-year survival rate was 0% for patients who stayed on insulin therapy and dialysis
[1]. An analysis of the Organ Procurement and Transplantation (OPTN) registries including 12,478 patients also reveals remarkable advantages of SPK transplantation. Data showed only a 58% four-year survival rate for patients on the waitlist, compared to a four-year survival rate of 90% after SPK
[17]. To put this in perspective, the survival time on the waiting list is worse than for patients with stage 3 colon cancer
[18]. Therefore, all patients with type 1 diabetes and impaired kidney function should be transplanted as soon as possible.

With this stark realization in times of organ shortage, new strategies to expand the donor pool are needed. Success in this regard has been realized with other organ transplants. For instance, the use of ‘marginal’ or ‘extended’ criteria donor organs is well established now, such as the so-called European Senior Donor Program for kidneys. Here, the potential higher risk associated with an older organ was compensated by the benefit of a short ischemic time through a change in the allocation system to only regional allocation
[19,20]. Regarding pancreas transplantation, there are different factors that have to be considered when trying to expand the donor pool. There are data from other allocation areas throughout the world (United Network for Organ Sharing (UNOS) or UK) that a good overall outcome after pancreas transplantation can be achieved with donors exceeding the standard allocation criteria as currently defined by ET, if the cold ischemic time is kept short. In Great Britain, a local retrieval and allocation system was established in 2000
[21], resulting in a steep increase in pancreas transplantation
[22,23] via extensive use of extended pancreas donors. These extended criteria avoid the donor BMI restriction and accept donors with an age between 8 and 68 years. Meanwhile 350 SPK and PTA were transplanted with an excellent one-year pancreas survival of 91%, kidney survival of 95% and a patient survival of 96%
[24].

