## Conclusions

The EXPAND study is the first prospective trial comparing and evaluating the outcome of standard criteria deceased donor pancreas organs to extended criteria organs. If our hypothesis, that EDC organs can be used with a similar outcome without additional risk for the patient is correct, the pancreas donor pool will successfully be expanded in the ET region. This will lead to more transplantations and shorter times on the waitlist with significantly reduced morbidity, increased life expectancy and better quality of life for many patients.

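### The stated hypothesis compares extended-criteria with standard organs, but the primary test compares the extended-criteria arm with a fixed 65% and so cannot support a conclusion of similarity

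*Protocol article*

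**What the plan says.** The question is put comparatively throughout the protocol article.

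- Abstract, Discussion: the hypothesis is that "locally allocated extended criteria organs can be transplanted with similar results compared to the currently allowed standard ET organ allocation".
- Background: EDC organs "can be transplanted with similar results compared to the standard criteria organs".
- Objectives and study concept: EDC organs, if transplanted regionally, "will have a similar function compared to organs with the currently allowed criteria".
- Conclusions: the hypothesis to be confirmed is that "EDC organs can be used with a similar outcome without additional risk for the patient".

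The primary analysis is not comparative. Under Sample size calculation, 55 EDC patients give 80% power to distinguish 65% from 80% three-month pancreas graft survival with a one-sided binomial test at 0.05. The 65% is a minimum acceptable rate agreed by the participating centres. Statistical analysis names the same test for the primary endpoint.

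The control arm has a different job: "The control group should be of equal size for analyzing the secondary endpoints". Statistical analysis places between-arm comparisons under the secondary endpoints, as two-sided tests at 0.05, and Sample size calculation says these were not powered. Pancreas graft function and survival are among those secondary endpoints (Objectives and study concept).

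**The concern.** Rejecting 65% shows that three-month EDC graft survival is above 65%. It says nothing about how EDC organs perform relative to standard organs transplanted in the same centres and period, because no control result enters the test. The comparative hypothesis is therefore left to a secondary test of difference. That test has no stated margin and no planned power, and its null result is not evidence of similarity.

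The stake is practical. The article's Discussion says that authorities are waiting for the trial before extending rescue allocation to the whole Eurotransplant area. If success on the primary endpoint were taken as confirmation of similarity, the policy would rest on a test that did not examine it.

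**Working it through.** **Inputs from the protocol article (Sample size calculation).** Null rate 65%, expected rate 80%, one-sided alpha 0.05, target power 80%, 55 EDC patients, control arm of equal size.

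**1. Reproduce the plan's figure.** For X ~ Binomial(55, p), find the smallest r with P(X ≥ r | 0.65) ≤ 0.05.
- r = 41: P = 0.087, too large.
- r = 42: P = 0.0489, accepted.
- Power: P(X ≥ 42 | 0.80) = 0.803.
- No sample size from 50 to 54 reaches 80% power.

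So 55 is correct for the test named, and it is reproduced without any control-arm input.

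**2. What success means.** 42/55 = 76.4%. The exact one-sided 95% lower limit is 65.07%, just above 65%. If true EDC survival is 80%, the success probability is 0.803 for every possible control rate.

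**3. What the controls could show at the same time.** The article gives no control-arm rate, so the control counts below are assumptions. EDC is held at the success boundary, 42/55. Intervals are Newcombe 95% limits for EDC minus control.

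| Controls | Control rate | Difference (points) | 95% CI | Fisher p | Primary test |
|---|---|---|---|---|---|
| 44/55 | 80.0% | -3.6 | -18.9 to 11.8 | 0.82 | succeeds |
| 50/55 | 90.9% | -14.5 | -28.3 to -0.5 | 0.069 | succeeds |
| 51/55 | 92.7% | -16.4 | -29.8 to -2.7 | 0.033 | succeeds |

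The primary verdict is the same in all three rows, although the comparative evidence differs widely.

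**4. How often the two results would conflict.** With true EDC survival at 80%, the chance of primary success together with a Fisher-significant deficit in the EDC arm is 0.2%, 1.5% and 9.7% for assumed true control rates of 80%, 85% and 90%.

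**5. What the between-arm comparison can deliver at 55 per arm.** Assume 80% in both arms.
- Standard error = √(2 × 0.80 × 0.20 / 55) = 0.0763.
- Half-width = 1.96 × 0.0763 = 0.150, or about ±15 points.
- Take a 15-point margin (80% minus 65%; the article does not state this as a between-arm margin). Then 0.15 / 0.0763 = 1.967.
- Power when the lower 95% limit must lie above -15 points: Φ(1.967 - 1.960) = 0.50.
- Power at one-sided 0.05: Φ(1.967 - 1.645) = 0.63.

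The result depends on the assumed rate. At one-sided 0.05, power is 71% with 85% in both arms and 84% with 90% in both.

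**The case against.** **The design is defensible in its own terms.** Randomisation is impossible because the organ offered decides the arm, and numbers per centre are low. A minimum acceptable rate, openly stated and agreed by the centres, is a legitimate primary criterion. This stands: neither the test nor the 55 is wrong. What the design does not support is a conclusion of similarity drawn from it.

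**The controls are used.** Pancreas graft survival is a secondary endpoint and is compared between arms. The detailed secondary strategy is left to a statistical analysis plan that is not shown, and its absence from an article is no fault. This also stands, so a reader who inferred that the trial ignores its control arm would be going too far: that is true of the primary test only. But the article does fix these comparisons as two-sided tests at 0.05 without a power analysis, and non-significance in such a test does not establish similarity.

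**The trial might succeed while EDC organs are clearly worse.** A reader might infer this from the Discussion's one-year pancreas survival of 91%. The documents do not support using that figure as the control rate. It is a one-year rate from a British programme that used extended donors extensively, and the same Discussion describes German outcomes as poorer than those of high-volume centres in the UK. At about that rate (50/55) the example is borderline, with Fisher p = 0.069. With controls at 80%, the deficit is 3.6 points and the interval spans zero. Conflict is possible, but it becomes appreciable only at control rates that the article does not give.

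**The article does not say that the primary test alone would settle similarity.** This is fair. It makes the policy step conditional on the hypothesis being correct, without saying which analysis decides that. The gap is the missing link between hypothesis and test.

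**Conclusion.** The concern holds in this limited form. The hypothesis and the intended conclusion are comparative, while the primary test is a one-sample test against 65% that succeeds at 42/55 whatever the control result. It cannot by itself support a claim of similar outcome or of no additional risk, and the secondary comparison as fixed in the article does not fill the gap.

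This mismatch needs no assumption about control rates. The size of any conflict does: the illustrated differences of -3.6 to -16.4 points rest on assumed control results of 80% to 93%. The precision of about ±15 points assumes 55 evaluable patients per arm and 80% survival in both. The power of about 50% for the confidence-interval rule also assumes a 15-point margin, which is inferred from 80% minus 65%.

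**What to change.** 1. State that a positive primary test concludes only that three-month EDC pancreas graft survival exceeds 65%.
2. Make the EDC-minus-control difference in three-month graft survival, with its 95% confidence interval, the key secondary analysis, in place of reliance on a two-sided significance test. Because allocation is not random, EDC organs are allocated regionally, and the centre offered an EDC organ chooses the recipient, add an estimate adjusted for baseline and donor data already collected. Donor age and BMI define the arms and so are not candidates. With 80% survival in both arms only about 0.20 × 110 = 22 graft failures are expected, so the covariate list must be short and named in advance.
3. Make any statement of similarity or absence of additional risk depend on that interval, read against a between-arm margin that the sponsor states and justifies. Fifteen points is a candidate, but the article gives 65% as an absolute floor and not as a margin against controls.
4. State the expected precision of about ±15 points. With a 15-point margin and 80% in both arms, also state the power: about 50% for the 95% interval rule, or about 63% at one-sided 0.05.

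The cost is narrower wording and one further pre-specified analysis, which can go into the statistical analysis plan before database lock. No extra patients or data are needed. The downside is that the interval may well be too wide to support a conclusion of similarity, and the trial would then have to say so.

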### Statistical analysis

A one-sided, binomial hypothesis test with a target significance level α = 0.05 and a target power 1−β = 0.80 will be used for analysis of the primary endpoint. The primary analysis will be based on the intention-to-treat (ITT) analysis set. However, a sensitivity analysis will be done on a per-protocol (PP) analysis set. The latter serves to assess the robustness of the results. All safety data will be analyzed by means of the safety population. For the secondary endpoints the treatment group will be compared to the control group, and all statistical tests will be two sided and will be done at the 0.05 significance level. The exact analyzing strategies of all secondary endpoints will be further specified in a Statistical Analysis Plan, which will be finalized prior to database lock. The statistical analysis will be done by the Center for Clinical Studies at the University Hospital Regensburg.

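### A total of 120 does not keep 55 extended-criteria recipients at the stated 10% dropout; it leaves 54, a small arithmetic slip that makes the planned power slightly optimistic

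*Protocol article*

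**What the plan says.** In the Protocol article, section Sample size calculation, the primary endpoint is three-month pancreas graft survival in extended-criteria recipients. It is tested against a fixed minimum of 65%, "on the assumption that a rate of 80% can be expected". The error rates are explicit: "The significance level of alpha (one-sided) was set to 0.05 and beta was set to 0.20". The section says that exact binomial probabilities were used, and it attaches the power to one number: "A sample size of 55 patients with extended donor pancreas allografts achieves 80% power". The control group is to be equally large, for the secondary endpoints only. The total follows: "Assuming a maximal dropout rate of 10%, a total of 120 patients will be required".

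The section Statistical analysis names the analysis set: "The primary analysis will be based on the intention-to-treat (ITT) analysis set". A per-protocol analysis serves as sensitivity analysis. Neither section says how a patient without a known three-month graft status is counted.

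**The concern.** The only purpose of a dropout allowance is that the required number remains after the stated loss. Here it does not: the allowance leaves one patient fewer than the calculation calls for.

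One patient would hardly matter if power changed smoothly with sample size. With an exact binomial test it moves in a sawtooth, and 55 is a favourable number while 54 is not. This is the only powered test in the trial, since the section says that no power analysis was done for secondary endpoints. If the result is not significant, readers will use the stated power to judge how far it counts against extended-criteria organs.

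**Working it through.** **Inputs**, all from Sample size calculation: null rate p0 = 0.65; expected rate p1 = 0.80; one-sided α = 0.05; target power 0.80; n = 55 in the extended-criteria arm; control arm of equal size; dropout at most 10%; total 120.

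**Test.** For each n, take the smallest c with P(X ≥ c | n, 0.65) ≤ 0.05. Power is P(X ≥ c | n, 0.80).

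**Step 1: the plan's own figure.** For n = 55, c = 42, attained α = 0.0489 and power = 0.8032. The stated 80% is reproduced. The normal approximation agrees: n = [(1.645 × √(0.65 × 0.35) + 0.842 × √(0.80 × 0.20)) / 0.15]² = 55.9.

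**Step 2: the dropout allowance.**
- Per arm: 120 / 2 = 60.
- Left after 10% loss: 60 × 0.9 = 54, which is below 55.
- Loss that 60 can absorb: (60 − 55) / 60 = 8.3%.
- Enrolment needed for 10% loss: 55 / 0.9 = 61.1, so 62 per arm and 124 in total.

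**Step 3: exact power at the numbers that may be analysed.**

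| n analysed | c | attained α | power at 80% |
|---|---|---|---|
| 54 | 42 | 0.0307 | 72.6% |
| 55 | 42 | 0.0489 | 80.3% |
| 56 | 43 | 0.0406 | 78.3% |
| 57 | 44 | 0.0335 | 76.2% |
| 58 | 45 | 0.0276 | 74.0% |
| 59 | 45 | 0.0436 | 81.2% |
| 60 | 46 | 0.0362 | 79.3% |
| 62 | 47 | 0.0465 | 83.8% |

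**Step 4: random loss.** The number left will not be exactly 54. If each patient is lost independently with probability 10%, and power is averaged over Binomial(N, 0.9), the result is 75.5% for N = 60 and 76.7% for N = 62.

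**Step 5: how much of the dip at 54 is real.** At 54 the critical value stays at 42, so the attained α falls from 0.049 to 0.031 and power falls with it. The normal approximation, which has no such steps, gives about 78.7% at 54 and 79.4% at 55. The information lost with one patient is therefore worth less than one point; the rest of the 7.7-point drop (80.3 − 72.6) is discreteness.

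**The case against.** The strongest reply is that nothing material is wrong. The article ties 80% to 55 patients, and that is right. The 10% is a maximum, not an expectation. Five losses out of 60 leave 55 (80.3%), one loss leaves 59 (81.2%), and no loss gives 79.3%. Enrolling 62 would not guarantee 80% either: 62 × 0.9 = 55.8, and 56 patients give 78.3%. Type I error stays at or below 0.05 at every n, so the slip cannot produce a false claim of acceptability.

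Most of this stands, and it limits the point to a minor one. It does not remove it. A stated maximum is the case that an allowance is meant to cover, and 60 per arm does not cover it. Discreteness explains the dip, but the exact test is the one prespecified, so 72.6% is its actual power at 54.

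Two stronger readings are tempting. A reader might infer that the design never has 80% power; the table contradicts this at n = 55 and n = 59. A reader might also infer that allowing for dropout conflicts with an intention-to-treat primary analysis, or that dropouts will count as failures with a large loss of power. The article inflates enrolment but never says that dropouts leave the intention-to-treat set, and it contains no rule that counts them as failures. Such a rule is commonly left to the full protocol or the SAP, neither of which is shown. The section Follow-up plans a month-3 visit and records graft survival from routine data, so a known status for most patients is plausible.

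**Conclusion.** The point holds as a minor arithmetic error. The total of 120 falls two patients per arm short of what the stated 10% dropout requires (60 against 62). The power statement for 55 patients is correct, but it does not carry over in full to the planned enrolment: power is 79.3% with all 60 analysed, 72.6% if exactly 54 remain, and about 75.5% on average under random 10% loss.

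These figures assume a true survival rate of 80%, equal arms, the exact test with the critical value set for the number actually analysed, and, for the figures with loss, that patients without a three-month status leave the denominator and that loss is unrelated to outcome. No defect in the test, the 65% limit or the choice of analysis set follows from this.

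**What to change.** Keep 120 and change the wording in Sample size calculation. State that 60 extended-criteria recipients will be enrolled; that power is about 79% when all 60 are analysed under intention-to-treat (success declared at 46 or more surviving grafts); and that it falls to about 73–76% if 10% have no three-month graft status. If the section is to quote a total inflated for 10% dropout, the figure should be 124 (62 per arm).

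Keeping 120 needs no extra patients and no change to the test; the cost is a slightly less favourable stated power. Quoting 124 as the recruitment target would mean four more patients for a small gain, from 75.5% to 76.7% on average under random 10% loss.
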